## 1.

## 2. Introduction

### Intervention:

The study intervention (the PCC intervention) is a three-part, mutually supporting set of organizational change practices meant to improve patient experience, engagement in care and clinical outcomes. The three components are:

1. Assess the patient experience (e.g., satisfaction, barriers to care) and incorporation of these assessments into facility feedback mechanisms (e.g., retention and viral load);
2. Train and mentor health care workers in patient-centred principles and practices based on patient experience data;
3. Offering facility level incentives for progress and improvement in patient experience measures

### Study design:

We used a stepped wedge cluster randomised trial to assess the effect of the PCC intervention in 24 clinics. We introduced the intervention at four randomly-determined time points at study start, 6, 12 and 18 months. We followed all sites for a total of 24 months. The size of each sequence was not the same, with eight facilities in sequence 1, four in sequence 2, four in sequence 3 and eight in sequence four. The unequal weights allow us to power outcomes such as viral load that occur over periods of time that are longer than each period, and for which cross over would preclude comparison of each treatment condition.

## 2.0 Outcomes

### 2.1 Primary outcome

Treatment failure defined as a composite of any of the following:

- (1) Unsuppressed viral load (> 400 copies/ mL) 15 month after enrollment (window 11-19 months). We use the viral load measurement closest to 15 months of follow-up if multiple exist, or
- (2) documented disengagement in care (out of care during the 15-month follow up time point) if no viral load measurements are available, or
- (3) documented cessation or antiretroviral medication if no viral load is available, or
- (4) death at 15 months of follow up

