| Behavioural Target                                                                  | 
 
Knowledge and skills to deliver person-centred care
 
Increased salience, motivation, and identification of opportunities to deliver more person-centred care
 
Increased of PCC behaviors, including being more welcoming, empathy, improved communication, shared decision making, and leveraging discretionary power to better accommodate client needs.
 
 |
| Temporality                                                                         | 
 
Training HCW on PCC at 0m for Group 1, 7m for Group 2, 13m for group 3 and 19m for Group 4
 
Mentorship begins immediately after first batch of HCWs trained in PCC
 
Synthesis meeting 6 weeks after training
 
Client experience data review meetings every 3 months
 
Incentive for best performing facility every 6 months
 
                |
| Dose                                                                                | 
 
PCC training done once for two days for each HCW
 
Weekly mentorship visits to facility till study end
 
                                                                                                                                                                                                                                                             |

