## 3.0 – Primary Outcome - Treatment Failure

### Study Population:

The population for primary study endpoint will be our treatment failure cohort. This is comprised of a systematic sample of patients who meet the following inclusion criteria at the onset of the study, and for whom we collected additional information to be able to contact them at the end to try and ensure higher levels of outcomes ascertainment. The cohort enrollment was defined by:

- Adult accessing HIV care;
- made a visit to one of the Wave 1 or Wave 4 study facilities in the first 6 months (period 1) of the 24-month study period;
- ever been on ART (including those prescribed on that very visit), not planning on leaving the area, resident of the catchment area of the clinic, and
- we restrict to facilities in wave 1 and 4 in order to allow a minimum of 12 months of exposure the intervention or control conditions at the time out outcome assessment.

At each site the selection of patients for the primary outcome (viral load subcohort) included a quarter new on ART, a quarter lost or late, and half in care.

|                   | Period 1                                                                  | Period 2 | Period 3                     | Period 4 | Totals per wave |
|-------------------|---------------------------------------------------------------------------|----------|------------------------------|----------|-----------------|
| Wave 1            | Intervention
61 patients x 8 facilities =
488 patients total |          | Outcome Ascertainment |          | 488 patients    |
| Wave 2            |                                                                           |          |                              |          |                 |
| Wave 3            |                                                                           |          |                              |          |                 |
| Wave 4            | Control
61 patients x 8 facilities =
488 patients total      |          | Outcome Ascertainment |          | 488 patients    |
| Totals per period | 976 patients                                                              |          |                              |          | 976 patients    |

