- Treat viral load<40 and viral load<1000 as “Definite Success”
- Widen the window for viral load to 9 - 21 months.

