## 5.0 – Secondary Outcome – Retention in Care

### 5.1 – In Care at 15 months

**Outcome:** This secondary outcome for retention is being in care at 15 months which will be defined as not being more than 30 days late to a visit at 15 months. We will use EHR data (i.e., SmartCare) that includes sociodemographic, clinical, visit history, and pharmacy data to determine this outcome.

**Population:** The population for this outcome will include all individuals ( $\geq 18$  years old) who made a visit to one of the Wave 1 or Wave 4 study facilities in the first 6 months of the 24-month study period (i.e., period 1). We restrict to facilities in wave 1 and 4 in order to allow a minimum of 15 months of exposure to either the intervention or control conditions at the time out outcome assessment without crossover. This allows us to analyze this aim like a parallel cluster-randomized trial.

|                   | Period 1                                                                                   | Period 2 | Period 3                     | Period 4 | Totals per wave |
|-------------------|--------------------------------------------------------------------------------------------|----------|------------------------------|----------|-----------------|
| Wave 1            | Intervention
All individuals making visit to Facility during Period 1
~40,000 |          | Outcome Ascertainment |          | ~40,000         |
| Wave 2            |                                                                                            |          |                              |          |                 |
| Wave 3            |                                                                                            |          |                              |          |                 |
| Wave 4            | Control
All individuals making visit to Facility during Period 1
~40,000      |          | Outcome Ascertainment |          | ~40,000         |
| Totals per period | ~80,000                                                                                    |          |                              |          | ~80,000         |

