## **7.0 STEPPED WEDGE DESIGN**

Stepped-wedge cluster randomized designs are used when equipoise is not met (because the preponderance of evidence favours the intervention), but when there is also a desire for rigorous inference about the magnitude of the effect (50). We plan on evaluating approximately 34 facilities mainly in Lusaka Province which are between 500 and 10,000 patients currently on ART. We will roll out the intervention in four groups, at time zero, 6, 12 and 18 months, and follow all sites for a total of 24 months. We employ an open-cohort design where new patients can enter observation time at any time during the trial and be measured for outcomes at multiple times. Some measurements which are made repeatedly overtime, and in these cases, it is possible that a single patient if surveyed more than once can contribute to the patient experience or service delivery outcomes both before and after cross over. For other outcomes such as retention and viral load which represent cumulative effects of longitudinal exposure to the intervention, we will censor at crossover. Because we seek to detect both the impact of the intervention on the patient experience (which can occur over shorter term) as well as retention and viral load (over a longer term), we will weight the steps unequally to achieve adequate power in both types of outcomes. Specifically we seek to randomize approximately 75% of facilities to the first and last waves and 25% to waves two and three.

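### The 11-19 month viral load window runs up to 4 months past the control facilities' crossover, and the SAP has no rule that keeps those results out of the control arm

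*Combined protocol and SAP*

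**What the plan says.** **Window.** SAP section 2.1 takes the viral load "15 month after enrollment (window 11-19 months"). Where there is a choice, "We use the viral load measurement closest to 15 months of follow-up if multiple exist". The sensitivity analyses in SAP section 3.0 add "Widen the window for viral load to 9 - 21 months".

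**Enrolment.** Under SAP section 3.0 a patient qualifies who "made a visit to one of the Wave 1 or Wave 4 study facilities in the first 6 months (period 1").

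**Crossover rule.** Protocol section 7.0 states: "For other outcomes such as retention and viral load which represent cumulative effects of longitudinal exposure to the intervention, we will censor at crossover". SAP sections 2.1 and 3.0 contain no corresponding sentence. The SAP 3.0 table and Figure S1 do place outcome ascertainment in Period 3, when Wave 4 is still in the control condition.

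**Calendar.** The documents date the Wave 4 start in three ways:
- SAP, Study design: "We introduced the intervention at four randomly-determined time points at study start, 6, 12 and 18 months", with 24 months in total.
- Intervention description table: "Training HCW on PCC at 0m for Group 1, 7m for Group 2, 13m for group 3 and 19m for Group 4".
- Figure S1: periods of 6, 9, 6 and 6 months, 27 months in total, because Period 2 was extended during COVID-19. This puts the Wave 4 start at month 21.

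**The concern.** Waves 1 and 4 were chosen for the primary outcome so that it could be analysed as a parallel comparison of patients who stay in one condition. That holds only if each Wave 4 outcome is measured before the facility goes live. The window is counted from each patient's own enrolment and has no calendar limit, so it can run on after the control facility has become an intervention facility.

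A viral load taken then is partly an intervention outcome counted as control. If the intervention works, this pulls the arms together. The primary comparison has eight facilities per arm, so a null result would be harder to interpret.

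**Working it through.** **Inputs**
- Enrolment at study month e, from 0 to 6 (SAP 3.0, Study Population).
- Window e + 11 to e + 19 (SAP 2.1); sensitivity window e + 9 to e + 21 (SAP 3.0).
- Crossover month C = 21 (Figure S1).
- Assumption: enrolment is uniform over months 0-6. The documents give no enrolment curve.

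**Step 1: check the calendar.** 6 + 9 + 6 + 6 = 27 months, which reproduces the total in Figure S1. The visit dates in SAP section 4.0, 17 August 2019 to 17 November 2021, also span 27 months. Period 4, and so the Wave 4 intervention, starts at 6 + 9 + 6 = 21.

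**Step 2: span of the window.** Earliest 0 + 11 = 11, latest 6 + 19 = 25. The excess past crossover is at most 25 − 21 = 4 months. For the sensitivity window it is 6 + 21 − 21 = 6 months. An overlap also exists if C is taken as 19 (up to 6 months) or 18 (up to 7 months).

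**Step 3: patients whose window extends past crossover.** e + 19 > 21 when e > 2, so the share is (6 − 2)/6 = 67%. For 9-21 months, e + 21 > 21 for everyone enrolled after month 0.

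**Step 4: share of window time after crossover.**
- For e > 2 the excess is e − 2 months. Integrated from 2 to 6 this gives 8. Total window time is 6 × 8 = 48. Share 8/48 = 16.7%.
- For 9-21 months the excess is e. Integrated from 0 to 6 this gives 18. Total 6 × 12 = 72. Share 18/72 = 25%.
- Range for one patient in the main window: 0% if enrolled by month 2, rising to 4/8 = 50% if enrolled at month 6. Late-weighted enrolment would raise the average and early-weighted enrolment would lower it.

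**Step 5: the 15-month target.** The latest target date is 6 + 15 = 21, which does not pass crossover.

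**Step 6: illustrative dilution.** Take the SAP's 10.7-point detectable difference and 80% power at face value. Assume viral loads spread evenly over the window and an immediate full effect at go-live. Then 10.7 × (1 − 0.167) = 8.9 points. Power becomes Φ(2.80 × 0.833 − 1.96) = Φ(0.37), about 65%. Both assumptions are unfavourable to the plan, and the objection below gives reasons to expect less.

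**What cannot be computed.** Tables S10 and S11 show that 73 of 453 controls lacked an endline viral load, so 453 − 73 = 380 had one. How many of the 380 were dated after go-live is not reported.

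**The case against.** The strongest reply is that the documents, read together, intend measurement before crossover. The SAP table and Figure S1 put ascertainment in Period 3, and the SAP does not revoke the protocol's censoring rule. The closest-to-15-months rule also favours earlier results. Any post-crossover exposure is at most 4 months, within the SAP's early-intervention category (up to 6 months). There the SAP expects a lag, and the first data feedback came only at 3 months.

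This stands as an argument about size. It does not close the gap. The Period 3 box is a schematic, and a window covering calendar months 11-25 does not fit into months 15-21. The closest-to-15 rule works only when several results exist, and it can even select a late one: for a patient enrolled at month 6 with results at 13 and 16 months, it takes the latter, at calendar month 22.

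A reader might infer three stronger points, which the documents do not support.

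- **Half of the 15-month targets fall after crossover.** This pairs month 18 from the SAP's Study design text with the 15-month endpoint. Month 18 belongs to the planned six-month periods and the earlier 12-month target (6 + 12 = 18). The 15-month target goes with the extended Period 2 (6 + 15 = 21).
- **The retention outcome is contaminated.** SAP section 5.1 claims a "minimum of 15 months of exposure to either the intervention or control conditions at the time out outcome assessment without crossover". With crossover at month 21 this holds exactly, and that outcome has no 11-19 month window.
- **Exposure will be miscoded.** Coding from months 12 and 18 instead of 15 and 21 would mislabel 4 × 3 + 8 × 3 = 36 of 4 × 6 + 4 × 15 + 8 × 21 = 252 control facility-months (14%). No document plans this: SAP section 5.2 assigns each visit by when it occurred, and section 4.0 works with study periods.

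**Conclusion.** The point holds for the primary viral load outcome. As written, the SAP lets a Wave 4 viral load taken up to 4 months after go-live count as control, contrary to protocol section 7.0 and to the SAP's own Period 3 plan. The sensitivity window extends this to 6 months.

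The 67%, 17% and 25% rest on uniform enrolment and crossover at month 21. They describe where the window lies. They do not say how many patients were measured late, and it would be wrong to read 67% as a contamination rate. As a guide to the share of late viral loads, the 17% and 25% are upper-end, because the closest-to-15-months rule and the Period 3 plan both work against late results. The expected lag in effect further reduces the impact of any that remain.

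The likely direction is dilution toward no difference. The size is unknown and probably modest. The three calendars are a separate inconsistency of wording to be corrected; they do not show that exposure was miscoded.

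**What to change.** 1. In SAP sections 2.1 and 3.0, for the primary analysis, accept a Wave 4 viral load only if it is dated before that facility's actual go-live. Apply the same calendar cut-off in Wave 1, so that ascertainment stays symmetric.
2. Cap the 9-21 month sensitivity window at crossover in the same way.
3. Judge care status, cessation of ART and death as of the 15-month point. Allow evidence collected later if it concerns that point, since later tracing can validly establish it.
4. Report the number of Wave 4 viral loads dated after go-live, and keep the uncapped 11-19 month window as a sensitivity analysis.
5. Replace the three calendars (12/18 and 24 months; 13/19; 15/21 and 27 months) with one table of actual go-live dates, and code exposure from it throughout.

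**Cost.** Wording and one date filter. With crossover at month 21 every patient keeps at least months 11-15, and the mean window falls from 8.0 to 8 − 8/6 ≈ 6.7 months under uniform enrolment. Some late viral loads would be replaced by an earlier one or go to adjudication, adding to the 150 of 933 patients already without an endline result. The precision loss should be small, and the count in item 4 will show whether it is.

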## 2.2 Secondary outcomes

- Patient Experience from Trained Exit Client Surveys
- In Care at 15-month in care
- Missed next visit by 30 days

## 3.0 – Primary Outcome - Treatment Failure

### Study Population:

The population for primary study endpoint will be our treatment failure cohort. This is comprised of a systematic sample of patients who meet the following inclusion criteria at the onset of the study, and for whom we collected additional information to be able to contact them at the end to try and ensure higher levels of outcomes ascertainment. The cohort enrollment was defined by:

- Adult accessing HIV care;
- made a visit to one of the Wave 1 or Wave 4 study facilities in the first 6 months (period 1) of the 24-month study period;
- ever been on ART (including those prescribed on that very visit), not planning on leaving the area, resident of the catchment area of the clinic, and
- we restrict to facilities in wave 1 and 4 in order to allow a minimum of 12 months of exposure the intervention or control conditions at the time out outcome assessment.

At each site the selection of patients for the primary outcome (viral load subcohort) included a quarter new on ART, a quarter lost or late, and half in care.

|                   | Period 1                                                                  | Period 2 | Period 3                     | Period 4 | Totals per wave |
|-------------------|---------------------------------------------------------------------------|----------|------------------------------|----------|-----------------|
| Wave 1            | Intervention
61 patients x 8 facilities =
488 patients total |          | Outcome Ascertainment |          | 488 patients    |
| Wave 2            |                                                                           |          |                              |          |                 |
| Wave 3            |                                                                           |          |                              |          |                 |
| Wave 4            | Control
61 patients x 8 facilities =
488 patients total      |          | Outcome Ascertainment |          | 488 patients    |
| Totals per period | 976 patients                                                              |          |                              |          | 976 patients    |

## Timing of outcome ascertainment

At a target of 15 months, we will assess treatment failure. We use 15 months for practical reasons. Although our original target was to assess treatment outcomes at 12 months, we instituted an additional four-month period for ascertainment of viral load because 12 months after initial study start coincided with a period of health systems emergency in Zambia during the first wave of COVID-19 that led to a delay in study roll out (and extension of period two). We accept data for a 15-month endpoint using information in at a minimum approximately a six-month window around the 15-month point (11 to 19 months). This recognizes that we will be leveraging and using clinically obtained viral loads when possible, and the timing of such measurements may or may not coincide with observation time in this study.

## Outcome ascertainment process

If a patient does not have a viral load recorded in the interval of interest, we used an extended outcome ascertainment (EOIC) process. The EOIC process includes: intensive tracing to ascertain vital status and care status (informants to assess patient outcomes can include health care workers, community members, family and others). Information used all information about the patient and was adjudicated by a 7-team group (including physicians, nurses, and mentors) to assess whether individuals have evidence of being actively engaged in HIV care.

Based on EOIC, adjudication process, and viral loads; the primary outcome will be further characterized as:

1. "Definite success"
2. "Probable success"
3. "Probable failure"
4. "Definite failure"

Individuals with a documented suppressed viral load during the study outcome window (i.e., 11 to 19 months) are classified as "Define success". Individuals with a documented unsuppressed viral load or clear documentation of not taking medications as "Definite failure." Individuals who did not have a documented viral load during the study window were classified as either "Probable success" or "Probable failure" based on their prior viral load history, retention in care history (e.g., missed visits, running out of medications based on pharmacy records), and evidence of care based on tracing based on the adjudication process by 7 team members. For example if at 15 after randomization, no viral load outcomes were obtained, and a team found the patients who reported no care and stopping treatment, the patient would be classified as a definite failure. On the other hand, if the patient reported continuing in care and taking medications at an outside facility, even if it is one were not able to obtain viral load results from, and the visit history indicates continuous engagement, the patient would be classified as probable success.

Flowchart: Treatment outcome adjudication algorithm

[figure not shown]

